### Statistical analysis

All calculations for the planned number of cases were performed using the G*power 3.1 software (http://www.gpower.hhu.de) and StatMate (Graphpad, San Diego, USA). Data will be analysed with the latest version of the Graphpad prism software (Graphpad Software, San Diego, USA). A drop-out rate of 20% was calculated for the trial design and a minimum of 120 patients should be included. D'Agostino‐Pearson or Kolmogorov‐Smirnov test will be used for normality testing. Paired respectively unpaired student's t test will be used for metric and Wilcoxon-Mann–Whitney-Test will be used for non-metric data with regard to the primary and secondary endpoints.

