## Methods

### Hypothesis

We hypothesize that long-term, repetitive application of RIC in combination with best medical treatment (BMT) including systematic gait training and pharmacological standard therapy will lead to longer painless and total walking distance, better quality of life (QoL) and an enhanced ankle-brachial index (ABI), when compared to standard BMT therapy in the control group.

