### Patients

A total of 200 patients (minimal number to treat 120) with diagnosed PAOD Fontaine stage II b and aged over 18 years will be randomised if written consent is given.

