### Primary endpoints

Primary endpoint of the study is the improvement of the pain-free and total walking distance after RIC + BMT compared to BMT in the control group, respectively. The determination of the pain-free and total walking distance and classification according to the Fontaine classification stage I-IV will be assessed by a standardized treadmill-test at 3.2 km/h (2 miles/h) and an incline of 12% on the treadmill. Moreover, improvement of the ankle-brachial index (ABI) and the Quality of Life (QoL) will be determined by the SF-36 and VascuQoL-6-test (Fig. 1).

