### Follow-up

The trial will be supported by two study nurses respectively research assistants during the study course. Any complications will be recorded and additionally the patients will fulfil a mandatory study diary to increase compliance. At day 28 all patients will undergo a second treadmill test, ABI and final interviews for assessment of QoL (Fig. 2). Blood samples will be collected for further analysis of secondary endpoints. A further six months and twelve months follow-up will be provided by investigation of pain-free walking distance, ABI and again QoL to observe long-term effects of RIC in patients with PAOD.

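### The plan names paired and unpaired t tests for the primary endpoints without saying which decides, and does not use the baseline treadmill value as a covariate

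*Protocol article*

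**What the plan says.** The Hypothesis section expects longer walking distances "when compared to standard BMT therapy in the control group". The Primary endpoints section defines the endpoint as the "improvement of the pain-free and total walking distance", "after RIC + BMT compared to BMT in the control group". Both are contrasts between arms.

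The Statistical analysis section assigns the tests: "Paired respectively unpaired student's t test will be used for metric" data, and the Wilcoxon-Mann-Whitney test for non-metric data, "with regard to the primary and secondary endpoints". Two normality tests are listed just before this, with no stated consequence. The section does not say:

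- whether the paired or the unpaired test decides the primary endpoint;
- whether the unpaired test is applied to the day-28 distance or to the change from baseline;
- that baseline enters any model.

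A baseline value will exist, because the Follow-up section says: "At day 28 all patients will undergo a second treadmill test".

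**The concern.** A paired t test compares day 28 with baseline inside one arm. By the Hypothesis section, BMT includes systematic gait training, and both arms receive BMT. Improvement in each arm is therefore plausible with no effect of RIC, and a significant paired test in the RIC arm says nothing about RIC. Because the plan does not rank the two tests, it leaves room for that result to be reported as the primary finding.

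The unpaired test addresses the right question. As planned, however, it makes at best partial use of the strongest predictor of day-28 distance that the trial is likely to have, namely the same patient's baseline distance. What is at stake there is precision and power, not validity.

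**Working it through.** **No plan figure to reproduce.** The article gives no alpha, power, effect size, SD or correlation, so there is no power figure to check. The calculations below are illustrations.

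**Inputs from the article.** "A total of 200 patients (minimal number to treat 120"), 1:1 allocation and 20% drop-out. Evaluable: 200 × 0.8 = 160, or 80 per arm. The stated minimum of 120 is 60 per arm.

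**Assumed inputs.** Two-sided alpha 0.05; true between-arm difference 0.4 SD of walking distance; equal SD at baseline and day 28; correlation r between baseline and day 28 of 0.5 to 0.7.

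**Step 1: variance of the between-arm comparison, in units of the day-28 variance.**

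- t test on the day-28 value: 1
- t test on change: 2(1 − r)
- ANCOVA on baseline: 1 − r²
- ANCOVA relative to change: (1 − r²) / [2(1 − r)] = (1 + r)/2

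| r | Day 28 only | Change | ANCOVA | ANCOVA / change | ANCOVA / day 28 |
|---|---|---|---|---|---|
| 0.5 | 1 | 1.00 | 0.75 | 0.75 | 0.75 |
| 0.7 | 1 | 0.60 | 0.51 | 0.85 | 0.51 |

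Over a wider range of r, 0.3 to 0.9, ANCOVA has 65% to 95% of the change-score variance and 91% to 19% of the day-28 variance. For any r strictly between 0 and 1 it is below both.

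**Step 2: power.** The noncentrality is (0.4/√v) × √(n/2), where v is the variance factor and n the number per arm, referred to the noncentral t with 2n − 2 degrees of freedom. The one degree of freedom that ANCOVA spends on baseline is immaterial at this size. Example for n = 80, r = 0.5: change gives 0.4 × √40 = 2.53, power 71%; ANCOVA gives 2.53/√0.75 = 2.92, power 83%.

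| Evaluable | r | Day 28 only | Change | ANCOVA |
|---|---|---|---|---|
| 160 | 0.5 | 71% | 71% | 83% |
| 160 | 0.7 | 71% | 90% | 94% |
| 120 | 0.5 | 58% | 58% | 71% |
| 120 | 0.7 | 58% | 80% | 86% |

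**Step 3: what the paired tests would do if read as evidence for RIC.** Suppose that RIC has no effect and both arms improve equally by 0.3 SD of change (assumed). Each paired test then has power p = 0.755 with 80 per arm and 0.628 with 60 per arm. The chance that the RIC arm is significant and the control arm is not is p(1 − p): 0.755 × 0.245 = 0.185 and 0.628 × 0.372 = 0.234.

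A simulation with equal improvements of 0.1 to 0.3 SD of walking distance, r of 0.5 or 0.7 and 60 to 100 per arm gave about 3% to 26% for the same event. In the same runs the paired test in the RIC arm alone was significant in 12% to 97% of trials, while the unpaired test on change stayed at about 5%.

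**The case against.** The strongest reply is that the plan already contains a valid analysis. The endpoint is worded as improvement, so the natural reading is an unpaired t test on change, which uses baseline. In a randomised trial that test holds its 5% error rate, and chance baseline imbalance is covered by that rate. The sentence on tests is condensed and covers all endpoints; it may mean no more than paired for before-after and unpaired for between arms. The correlation and effect size are assumed, and at r = 0.7 the gain over change scores is only 90% to 94%.

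Most of this stands, and it rules out several stronger readings:

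- A reader might infer that baseline is ignored. The article does not say so. That would hold only if the day-28 value alone were tested, which the endpoint wording does not suggest.
- A reader might infer that significance in the RIC arm alone would count as success, with a false claim in up to a quarter of trials. Nothing in the article says that. The Step 3 figures depend on an assumed improvement and on misuse of the paired tests.
- A reader might infer that the t test is wrong because walking distance is skewed. The article gives no information on its distribution.
- A reader might infer that the normality tests decide nothing. Literally, the choice goes by metric or non-metric data, but their position suggests that they were meant to guide it.

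What the reply does not remove is that tests are fixed explicitly for the primary endpoints, the deciding one is not identified, and ANCOVA is more efficient than either version of the unpaired test.

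**Conclusion.** The point holds as one of ambiguity and lost efficiency, not of invalidity. The paired tests cannot answer the question that the trial poses, and the plan should say that they do not decide it. The unpaired test is valid, but ANCOVA would have 75-85% of its variance if it is run on change, or 51-75% if run on the day-28 value. At 160 evaluable that raises power from 71-90% (change) or 71% (day 28 only) to 83-94%; the gain is larger at 120 evaluable. The size rests on an assumed r of 0.5 to 0.7, a 0.4 SD effect and two-sided alpha of 0.05. The direction holds for any r strictly between 0 and 1. This should be changed, but the trial remains interpretable without it if the unpaired between-arm test is the one reported.

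**What to change.** - State one primary analysis: a between-arm ANCOVA of day-28 walking distance on arm and baseline distance, reported as the adjusted difference with a 95% CI, for pain-free and for total distance.
- Use the same model for pain-free distance at 6 and 12 months. It cannot be extended to total distance at those visits, because the Follow-up section lists only pain-free distance there.
- Label the paired within-arm tests as descriptive.
- Do not let a normality pre-test choose the primary test. Prespecify a log-scale or rank-based analysis as a sensitivity analysis. A log-scale model estimates a ratio rather than a difference in distance, so it should not silently replace the primary estimand.

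The cost is protocol and SAP wording and slightly more analysis work. No new data are needed. The change should be fixed before outcomes are compared by arm.

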### Follow-up

The trial will be supported by two study nurses respectively research assistants during the study course. Any complications will be recorded and additionally the patients will fulfil a mandatory study diary to increase compliance. At day 28 all patients will undergo a second treadmill test, ABI and final interviews for assessment of QoL (Fig. 2). Blood samples will be collected for further analysis of secondary endpoints. A further six months and twelve months follow-up will be provided by investigation of pain-free walking distance, ABI and again QoL to observe long-term effects of RIC in patients with PAOD.

### Trial status

After approval of the ethical committee of the University Hospital Schleswig–Holstein a first pilot study has been conducted prior to the main study. Currently 20 patients have been enrolled and the completion of the main trial is scheduled for December 2023.

## Discussion

Optimized treatment of PAOD remains a major and interdisciplinary challenge in current medicine [10]. Recent clinical studies have provided evidence that RIC could be a beneficial treatment option for cardiovascular disease in general but have also shown that large heterogenous trials and patient cohorts might not be the tools of first choice [5, 6, 8, 9]. Therefore, we here describe a trial design that will clarify the potential influence of RIC on relevant outcome parameters and QoL in patients with PAOD stage II Fontaine. Until today, only a few clinical studies have investigated the potential influence of RIC on PAOD with a limited number of patients and single respectively limited treatments [5, 6]. In contrast we hypothesised that chronic, repeated application of RIC might be necessary to generate PAOD-related therapeutic effects such as angiogenesis and collateral growth based on the knowledge that cardiovascular remodelling is often based on repeated stimuli [11, 12]. We have therefore conducted a study design that includes 3 × 5 RIC cycles per treatment day over a time period of 28 days. To the best of our knowledge this will be the first study to investigate this kind of repetitive RIC treatment in patients with PAOD.

A particular strength of this study might be the close monitoring of the patients during the trial which is represented by the employment of study nurses/research assistants providing weekly telephone/video feedbacks and a study diary. These aspects could be key factors to increase compliance and avoid the relatively high dropout rates described in similar trials [13].

Further, the here described study design not merely includes the clinical evaluation of the study patients but also conducts an experimental set-up taking into account the analysis of pro-angiogenetic protein levels and cellular transformation of mononuclear cell lines potentially influenced by RIC treatments [14, 15]. Accordingly, this study will provide insights not only in clinical outcome but also in molecular mechanisms associated with the effects of RIC treatment [16]. This monocentric trial design might represent a blueprint to enable further potential multicentric studies in patients with PAOD undergoing repetitive RIC application.

## Data Availability

All relevant data is included in the manuscript.

## Abbreviations

ABI: Ankle-brachial index
BMT: Best medical treatment
FC: Flow cytometry
PAOD: Peripheral arterial occlusive disease
RIC: Remote ischemic conditioning
QoL: Quality of life
